### Recruitment

Eligible patients from across Canada and their partners are being identified and informed about the study by their health care providers at collaborating institutions in Ontario, Nova Scotia, Manitoba, and British Columbia. In our pilot study, we found that active forms of recruitment enhanced enrolment. Patients who have been approached by their health care provider and express an interest in learning more about the program are asked for consent to have their contact information forwarded to the RC, who then follows up with the potential participant by phone to provide her (or him) with information about the program. Additionally, flyers are displayed across various hospitals and cancer agencies. Announcements have been made at hospital meetings, BC support groups, and community cancer related workshops for young women. The advertisement is posted on websites commonly accessed by young women with BC, social media, and the Couplelinks informational webpage that is linked to these.

### Procedure

Once a potential participant (typically the patient rather than the well partner) connects with the RC, she is informed about the nature of the project. This potential participant is asked to discuss the project with her partner and, if both are interested, the RC proceeds with scheduling a phone interview with each partner separately to confirm whether they both meet eligibility criteria. When screening couples, in addition to the inclusion and exclusion criteria previously described, the RC assesses partners’ access to, and comfort with, the internet and whether they are likely to be able to keep up with the weekly time commitment for the program. Partners who anticipate interruptions (for instance due to travel) for a duration longer than two weeks are asked to delay enrolment until after they return. To avoid the confounding effects of other interventions, couples are informed of the expectation that they refrain from participating in couple-related psychosocial interventions until they have completed the five-month study term.

If both participants meet the eligibility criteria, the RC proceeds with the informed consent process over the phone, which includes reviewing the objectives of the study, requirements of the participants, how their information will remain confidential, and participants’ right to withdraw at any time. Any concerns or questions are addressed and if the couple is satisfied, they are told they will be mailed a hard copy of the consent form that we request they review, sign, and return and that they may contact the RC again if they have any further questions. Once the signed informed consent form is received, the couples are randomized to the waitlist or intervention condition.

Next, each partner is separately emailed a unique personal login ID and password which they use to complete all questionnaires, starting with the baseline questionnaires. The couples in the treatment group complete additional questionnaires as described in the measurement section below. Participants are informed that their responses to the surveys will not be shared with their partner, and they are instructed to complete the surveys without consulting one another. Once the time one (T1) measures are completed, the RC informs participants of their group assignment. Participants assigned to the treatment group are informed of the name of their Couplelinks facilitator. The facilitator schedules a phone meeting with the couple to introduce her or himself, clarify expectations of participants, answer questions, and review important information about the website and the intervention. The facilitator then sends the couple their login instructions via email.

Both groups of participants complete standardized questionnaires online at T1, time two ((T2) at post-treatment for treatment and for waitlist groups, taking place eight weeks after T1), and time three ((T3) three months after completion of T2 measures). Participants in the treatment group are also asked to complete a post-treatment interview at T2. Couples in the waitlist group are given the option of receiving the intervention once they have completed the T3 questionnaires; if they choose to participate in the intervention, their completed T3 questionnaires will be used as their pre-treatment (baseline) measurement, and they will be asked to complete surveys at post-treatment and one last time 3 months after posttreatment.

### Measurement

The primary outcome of this study is improvement in relationship adjustment and dyadic coping. Secondary outcomes include improvement in mood (for example, anxiety or depression) and interpersonal communication. Self-reported socio-demographic variables are collected at T1 including: gender, age, ethnicity, education, employment status, relationship status, living arrangement, and number and gender of children. Self-reported disease and treatment information includes cancer stage, treatments received, status of treatment, and other health conditions. The assessment of the intervention’s effectiveness incorporates the effects of attrition and non-compliance into the analyses. Satisfaction with the intervention is assessed using a self-report questionnaire designed specifically for this study, and feedback for further improvements is obtained using a phone interview completed post-treatment. See Figure 1 for a flowchart of the trial with time points and corresponding measures.

**Figure 1 Fig1:**
[figure not shown]
**Flowchart of a randomized controlled trial (RCT) of Couplelinks.**
^1^Outcome Questionnaires include: BCRM = Breast Cancer and Relationship Measure, DCI = Dyadic Coping Inventory, FACT-B = Functional Assessment of Cancer Treatment - Breast (female only), HADS = Hospital Anxiety and Depression Scale, KMSS = Kansas Marital Satisfaction Survey, MMQ = Maudsley Marital Questionnaire, RDAS = Revised Dyadic Adjustment.

The Revised Dyadic Adjustment Survey (RDAS) [99] is an abbreviated version of the longer and widely used Dyadic Adjustment Survey (DAS) [100], with comparable levels of reliability and validity. This 14-item measure assesses dyadic consensus, cohesion, and satisfaction. The Kansas Marital Satisfaction Scale (KMSS) [101] is one of the most commonly used global measures of marital satisfaction. It is comprised of three items on a seven-point Likert scale, asking respondents to identify their level of satisfaction with their partner, their marriage, and their relationship with their partner. Both the RDAS and the KMSS have demonstrated reliability and validity, and empirically derived cut-offs to differentiate between samples of couples being seen for couple intervention versus a community sample. The marital adjustment subscale of the Maudsley Marital Questionnaire (MMQ) [102] evaluates an individual’s satisfaction with his or her committed or married relationship. It has 10-items, each rated on a nine-point scale.

The Hospital Anxiety and Depression Scale (HADS) [103] is a 14-item four-point Likert scale measure that includes two subscales of seven items each, assessing anxiety and depression. It is a simple yet reliable and valid tool to assess the presence of a mood disorder in medical settings. Although developed for a hospital-based population, it has also been found to be a valid screening instrument for depression and anxiety in the general population [104]. The Functional Assessment of Cancer Therapy-Breast (FACT-B) - Physical Well-Being (PWB) [105] subscale is part of the widely used FACT-B that assesses quality of life among breast cancer patients. The PWB, a seven-item five-point Likert scale measuring physical functioning, is completed by the female partner only. This variable will be tested as a potential covariate. The Breast Cancer and Relationship Measure (BCRM) was developed by the study authors for this protocol to assess the degree to which partners experience breast cancer to have negatively affected their relationship. The scale has 10 items which participants rate on a scale from 0 (not at all) to nine (very much) depending on the degree to which each statement applies to them. An example item is ‘We are able to discuss difficult or sensitive issues related to breast cancer’.

The Dyadic Coping Inventory (DCI) [106] is a 37-item questionnaire that measures levels of stress-related communication and levels of supportive and negative dyadic coping behaviors when one or both partners are stressed, as well as perception of one’s partner’s stress-related communication and support. The scale consists of seven subscales, with four measuring self and partner stress communication, and supportive, negative, and joint dyadic coping. Additionally, two items capture the quality of the self-perceived level of overall dyadic coping. The Credibility Expectancy Questionnaire (CEQ) [107] is a six-item survey that assesses the participants’ expectations about how beneficial they believe the treatment will be, and how reasonable it is in their view that the treatment will address their problem. The questionnaire consists of two parts to evaluate such expectations and perceptions, with one part asking participants to answer the questions based on their rational thought process, and the other section in which they are asked to answer based on their emotions. The original measure assessed changes in trauma symptoms. The wording of the measure in this study refers to changes in relationship adjustment. This measure is administered to the treatment group at T1 only.

The System Usability Scale (SUS) [108] is a 10-item measure designed to capture the participant’s subjective, global perspective of the website’s usability, including the website complexity and the perceived need for support or training. This measure is administered to the intervention group at T2 only. The Treatment Satisfaction Survey (TSS) measure was developed specifically for this study and assesses the satisfaction of participants in the intervention group with the program overall and specific aspects of it (for example convenience and facilitator role). In addition to items requiring quantitative ratings, open-ended questions are asked regarding the general experience, the program’s perceived benefits, and areas for improvement. The purpose of this measure is to obtain feedback regarding different facets of Couplelinks, in order to inform program development and determine participants’ perceptions regarding the effective and less effective aspects of program experience. This measure is administered once at T2 to the intervention group. After completing the T2 questionnaires, a semi-structured interview designed specifically for this study is conducted over the phone with couples in the intervention group to get more detailed feedback about the intervention. Both partners are interviewed together and the interview takes 40-60 minutes.

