### Sample size estimation and data analyses plan

All scale and subscale means and standard deviations will be computed and summarized. The primary hypotheses to be tested are that the degree of change or improvement between T1 and T2 on the RDAS, KMSS, MMQ, and DCI summary scales will be greater for the treatment group relative to the waitlist group. Given that data are non-independent (measurements are of individuals that belong to the same dyad and multiple measures are taken per individual across time) the hypotheses will be evaluated using multilevel models (MLM) [109]. MLM will allow for testing correlations between partners’ outcomes and whether there are differences in treatment effect for the patient versus her partner. The models will also be used to evaluate the degree of sustained change from T2 to T3, and whether treatment effects vary by severity of disease, age, and/or length of relationship, as well as aspects of the intervention such as level of engagement. MLM will also allow us to test whether there are any significant variations in treatment effect between facilitators. The impact of missing data will also be evaluated.

The sample size needed was based upon psychometrics of our primary outcome measure, the RDAS. Assuming a two-sided test, a standard deviation for mean change in RDAS from T1 to T2 equal to 3.4 (standard deviation of RDAS = 7.0, with a correlation of 0.9 between T1 and T2), an intracluster correlation of 0.3, an effect size of 0.5 for mean change of RDAS (difference in group means = 1.8), 80% power, and an alpha of 0.05, 36 couples will be required for each group (PASS, NCSS, Kaysville, USA, cluster-randomization power analysis) [110]. The total sample size was calculated as 36 × 2 × 2 = 144. The sample size will be increased to 160 (40 couples per group) due to an expected attrition of 10% of the participants across time, based on previous research in couples and BC [111]. In addition to the questionnaires, qualitative data will be collected from the open-ended evaluation of each DLM following its completion.

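### Randomisation precedes baseline and only the treatment arm gets the expectancy questionnaire at T1, so a baseline meant to be blind to allocation differs by arm and could signal it

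*Protocol article*

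**What the plan says.** The order of events is in the protocol article under Procedure. Randomisation comes first: "Once the signed informed consent form is received, the couples are randomized to the waitlist or intervention condition". Baseline follows: "Next, each partner is separately emailed a unique personal login ID and password which they use to complete all questionnaires, starting with the baseline questionnaires". That same section says "The couples in the treatment group complete additional questionnaires as described in the measurement section below", and it then sets the safeguard: "Once the time one (T1) measures are completed, the RC informs participants of their group assignment". Partners are also told that their answers will not be shared with each other and that they should not confer.

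The Measurement section describes the CEQ as a six-item survey that "assesses the participants’ expectations about how beneficial they believe the treatment will be", and says of it: "This measure is administered to the treatment group at T1 only". The other instruments given to the treatment arm alone (the usability scale, the satisfaction survey and the interview) are placed at T2. The CEQ is therefore the one arm-specific instrument that the text places at T1.

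Under Sample size estimation and data analyses plan, the primary hypotheses concern "the degree of change or improvement between T1 and T2 on the RDAS, KMSS, MMQ, and DCI summary scales". All four are self-report scales.

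**The concern.** The protocol intends participants to complete T1 without knowing their arm. It then puts into T1, for one arm only, a questionnaire about how much the treatment is expected to help. A participant who meets it before the outcome scales, or who hears of it from a partner, may guess the allocation and answer those scales differently. Relief at being treated soon could raise T1 scores, and a wish to show room for improvement could lower them.

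Because the primary contrast is change from T1, a shift in one arm's T1 mean moves the estimated effect by the same amount. Adjusting for T1 in the model would not remove it.

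The same ordering has a second consequence. A couple that is randomised and never completes T1 belongs to the randomised set but has no change score.

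**Working it through.** **1. The plan's own figure.** Inputs from Sample size estimation and data analyses plan: "a standard deviation for mean change in RDAS from T1 to T2 equal to 3.4", target difference 1.8, intracluster correlation 0.3, two-sided alpha 0.05, power 80%, 36 couples per group.

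- Design effect for couples: 1 + (2 − 1) × 0.3 = 1.3.
- Individuals per arm before clustering: 2 × (3.4 × (1.960 + 0.842) / 1.8)² = 56.0.
- With clustering: 56.0 × 1.3 = 72.8 individuals, or 36.4 couples. With 36 couples the power is 79.6%.

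The stated 36 is reproduced to rounding, so these inputs can be used to scale the concern.

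**2. Scale of the target.** The RDAS standard deviation (SD) is given as 7.0, so the target is 1.8 / 7.0 = 0.26 SD. A small shift in T1 level is therefore a sizeable share of the effect sought.

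**3. Illustrative shifts.** The documents give no figure for a T1 shift. The sizes below are assumptions, and they are averages over the whole arm.

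- 0.05 SD: 0.05 × 7.0 = 0.35 points; 0.35 / 1.8 = 19% of the target.
- 0.1 SD: 0.1 × 7.0 = 0.7 points; 0.7 / 1.8 = 39% of the target.

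**4. Effect on the test.** With 36 couples (72 individuals) per arm, the standard error (SE) of the difference in change is 3.4 × √(1.3 × 2 / 72) = 0.646. Rejection with no true effect is P(Z > 1.96 − b/SE) + P(Z < −1.96 − b/SE). Power when the shift opposes the treatment is P(Z < (1.8 − b)/SE − 1.96).

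| Assumed shift b | b / SE | Rejection, no true effect | Power if shift opposes treatment |
|---|---|---|---|
| 0 | 0 | 5% | 79.6% |
| 0.35 | 0.54 | about 8% | about 61% |
| 0.7 | 1.08 | about 19% | about 40% |

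**5. Direction.** Change is T2 minus T1. A lower T1 in the treatment arm inflates the apparent gain, and a higher T1 hides a real one. Nothing in the text favours either.

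**6. Dilution.** If only a fraction of the arm infers its allocation in time, the arm mean moves by that fraction of the individual shift. If half did so, an arm-wide 0.7 would need 0.7 / 0.5 = 1.4 points in each of them.

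**7. Baseline adjustment.** With the stated T1–T2 correlation of 0.9 and equal SDs at both times, the slope on T1 is 0.9. Adjustment then leaves 0.9 × 0.7 = 0.63 of a 0.7-point bias, that is 90%.

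**8. What a comparison of T1 means can show.** If the correlation of 0.3 also applies to T1 levels (an assumption), the SE of the T1 difference is 7.0 × √(1.3 × 2 / 72) = 1.33, and the 95% half-width is 1.96 × 1.33 = 2.6 points. The comparison would reveal a gross imbalance but not a 0.7-point shift.

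**The case against.** The strongest reply is that harm depends on a sequence the text does not give. The CEQ is placed at T1 without saying whether it comes before or after the outcome scales. Figure 1 could not be read here and may settle this; its footnote lists the outcome questionnaires without the CEQ. If the CEQ comes last, that participant's own scores are already recorded. The partner route is addressed by the instruction not to confer, and the text says that partners are emailed separately, not that they finish at different times. The signal is also weak: nothing says participants know that the other arm gets no CEQ, and waitlist couples are offered the programme after T3. All of this stands. It limits how likely and how large a shift would be, but it does not remove the conflict between withholding assignment and giving an arm-specific questionnaire.

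Four stronger readings are tempting, and the documents do not support them:

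- **That baseline was contaminated.** The text shows a route, not an occurrence.
- **That losses before T1 break the randomised comparison.** Those couples leave before being told their arm, so the loss should be largely non-differential unless the CEQ signal works. The plan also says that attrition will be incorporated into the analyses and the impact of missing data evaluated.
- **That the research coordinator biases T1.** The article does not say whether the coordinator knows the arm at that point. T1 is completed online under personal logins, and no mechanism is apparent.
- **That every change analysis is affected.** Sustained change from T2 to T3 does not use T1.

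**Conclusion.** The point holds as a design weakness that should be fixed, with moderate confidence. The text establishes that randomisation precedes T1, that the T1 battery differs by arm, and that this works against the stated intent to withhold assignment until T1 is done. The exposure is confined to contrasts that start from T1, which include all four primary scales.

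The size is unknown. The 19% to 39% of the 1.8-point target rests wholly on an assumed arm-wide shift of 0.05 to 0.1 SD, could run in either direction, and shrinks in proportion if few participants infer their arm in time. If the CEQ came after the outcome scales and partners did not confer, the shift by this route would be nil. Losses before T1 chiefly cost precision, but they should be visible.

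**What to change.** For couples not yet enrolled:

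- Randomise only after both partners have submitted T1.
- Give the CEQ either to both arms, or to the treatment arm after disclosure and before module 1.

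For couples already enrolled (Trial status gives recruitment since April 2011), the order cannot be changed. For them:

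- State where the CEQ fell in the T1 sequence. This is the most informative item: if it came after the outcome scales, only the partner route remains.
- Report, by arm, the number of couples randomised without a completed T1.
- Compare T1 means by arm, with confidence intervals, and do not read the absence of a significant difference as proof of no shift.

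The cost is a short delay between T1 and assignment. No new instrument is needed. Giving the CEQ to both arms would add six items for waitlist couples; moving it after disclosure adds none.

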### Sample size estimation and data analyses plan

All scale and subscale means and standard deviations will be computed and summarized. The primary hypotheses to be tested are that the degree of change or improvement between T1 and T2 on the RDAS, KMSS, MMQ, and DCI summary scales will be greater for the treatment group relative to the waitlist group. Given that data are non-independent (measurements are of individuals that belong to the same dyad and multiple measures are taken per individual across time) the hypotheses will be evaluated using multilevel models (MLM) [109]. MLM will allow for testing correlations between partners’ outcomes and whether there are differences in treatment effect for the patient versus her partner. The models will also be used to evaluate the degree of sustained change from T2 to T3, and whether treatment effects vary by severity of disease, age, and/or length of relationship, as well as aspects of the intervention such as level of engagement. MLM will also allow us to test whether there are any significant variations in treatment effect between facilitators. The impact of missing data will also be evaluated.

The sample size needed was based upon psychometrics of our primary outcome measure, the RDAS. Assuming a two-sided test, a standard deviation for mean change in RDAS from T1 to T2 equal to 3.4 (standard deviation of RDAS = 7.0, with a correlation of 0.9 between T1 and T2), an intracluster correlation of 0.3, an effect size of 0.5 for mean change of RDAS (difference in group means = 1.8), 80% power, and an alpha of 0.05, 36 couples will be required for each group (PASS, NCSS, Kaysville, USA, cluster-randomization power analysis) [110]. The total sample size was calculated as 36 × 2 × 2 = 144. The sample size will be increased to 160 (40 couples per group) due to an expected attrition of 10% of the participants across time, based on previous research in couples and BC [111]. In addition to the questionnaires, qualitative data will be collected from the open-ended evaluation of each DLM following its completion.

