**Methods/Design:**

A total of 80 heterosexual couples from across Canada in which the female partner has been diagnosed with a primary breast cancer will be recruited and randomized to a treatment or waitlist control group. Six dyadic learning modules form the core of the program and will be undertaken on a weekly basis. The manualized online intervention involves psycho-education and experiential exercises to enhance communication, coping ability, mutual empathy, and perspective-taking in relation to cancer. An online facilitator who is a trained mental health professional will guide and support couples throughout the process. Data collection will occur at baseline, at post-treatment or eight weeks into the waiting period, and at the three-month follow-up assessment. Primary outcome measures include the Revised Dyadic Adjustment Survey (RDAS) and Dyadic Coping Inventory (DCI) scores, and secondary outcome measures include the Hospital Anxiety and Depression Survey (HADS) score.

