### Hypotheses

We hypothesize that women and their male partners who participate in the Couplelinks program will demonstrate significant improvement on measures of relationship adjustment and satisfaction, dyadic coping, and intimacy, and measures of psychological distress and adjustment, as compared to participants in the control condition.

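### The primary outcome is not defined consistently: the trial is sized on RDAS alone, but the primary hypotheses cover four scales and the abstract names two

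*Protocol article*

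**What the plan says.** The protocol article describes the primary outcome in three places, and the descriptions do not agree.

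- **Abstract, Methods/Design:** "Primary outcome measures include the Revised Dyadic Adjustment Survey (RDAS) and Dyadic Coping Inventory (DCI) scores". The Measurement section says the same in terms of constructs: "The primary outcome of this study is improvement in relationship adjustment and dyadic coping".
- **Sample size estimation and data analyses plan, first paragraph:** the primary hypotheses are that "improvement between T1 and T2 on the RDAS, KMSS, MMQ, and DCI summary scales will be greater for the treatment group" than for the waitlist group. That is four scales.
- **Same section, second paragraph:** "The sample size needed was based upon psychometrics of our primary outcome measure, the RDAS". Here there is one primary measure, and the calculation uses it alone.

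The calculation is two-sided, with alpha 0.05, 80% power, a difference of 1.8, a change SD of 3.4 and an intracluster correlation of 0.3. It gives 36 couples per group, raised to 40 for 10% attrition. No alpha or power is given anywhere for KMSS, MMQ or DCI.

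**The concern.** The primary outcome decides whether the trial has succeeded, and the error rate and power describe that decision. Two of the three descriptions stand in adjacent paragraphs of one section, one plural and one singular. A separate analysis plan can settle how several primary outcomes are tested, but only once the set is fixed, and the article fixes it in more than one way. This is therefore a conflict in the printed text and not a detail deferred to another document.

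The Discussion says that, if shown to be effective, the program would be disseminated as an empirically validated tool. With the primary outcome open, that claim could rest on whichever scale shows a difference, while the design figures apply to only one of them.

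**Working it through.** **Inputs** (all from Sample size estimation and data analyses plan): difference 1.8; change SD 3.4; intracluster correlation 0.3 with two partners per couple; two-sided alpha 0.05; power 80%; 36 couples per group; attrition 10%.

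**Step 1: reproduce the plan's figure for RDAS.**
- Individuals per arm, ignoring clustering: 2 × [3.4 × (1.960 + 0.842) / 1.8]² = 56.0.
- Design effect: 1 + (2 − 1) × 0.3 = 1.3. So 56.0 × 1.3 = 72.8 individuals, or 36.4 couples per arm, against 36 stated.
- Power at 36 couples (72 individuals) per arm: the standard error is 3.4 × √1.3 × √(2/72) = 0.646, and 1.8 / 0.646 = 2.79. Power is 79.6% by the normal approximation and 78.5% by a t test with 70 df.
- Attrition: 36 / 0.9 = 40 couples, as planned.

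The 5% and 80% therefore hold for RDAS alone. (The RDAS inputs do not fully agree with one another: SD 7.0 with correlation 0.9 gives a change SD of √(2 × 49 × 0.1) = 3.13, and 1.8 / 3.4 is 0.53, not 0.5. That is a separate matter; the check here uses the stated 1.8 and 3.4.)

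**Step 2: apply the same design to two or four primary scales.** The article gives no effect size, SD or correlation for the other scales. I assume they share the RDAS values and let the correlation between scales run from 0 to 0.8. Correlated cases were simulated with 1,000,000 draws each.

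| Success rule | Quantity | Two scales | Four scales |
|---|---|---|---|
| Any scale at 0.05, unadjusted | Family-wise error | 7.8% to 9.75% | 11.4% to 18.5% |
| Bonferroni (0.025 or 0.0125 each) | Power per scale, 36 couples/arm | 69–71% | 59–61% |
| All scales at 0.05 | Power (error at most 5%) | 63–72% | 40–65% |

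- Any-of, independent scales: 1 − 0.95² = 9.75%; 1 − 0.95⁴ = 18.5%. The lower ends are at correlation 0.8.
- Bonferroni: the t-based values are 68.9% and 58.9%; the normal values are 70.7% and 61.3%. Holding 80% per scale would need 45 or 52 couples per arm, or 50 or 58 after 10% attrition, against 40 planned.
- All-of, independent scales: 0.796² = 63%; 0.796⁴ = 40%. The upper ends are at correlation 0.8.

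**Step 3: check which RDAS endpoint matches the sample size.** The calculation is for change from T1 to T2. An unadjusted RDAS difference at T2 has SD 7.0, so its standard error is 7.0 × √1.3 × √(2/72) = 1.33. Then 1.8 / 1.33 = 1.35, and power is about 27%. RDAS at T2 adjusted for baseline has a residual SD of 7.0 × √(1 − 0.9²) = 3.05, which is no larger than the 3.4 assumed. Change or baseline-adjusted T2 therefore fits the sample size; raw T2 does not.

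**The case against.** The strongest reply is that the descriptions differ less than they seem to. The abstract uses open wording for its list, and relationship adjustment in the Measurement section could be read to cover RDAS, KMSS and MMQ. That stands in part: the two-outcome and four-scale descriptions can be read together. Neither can be read together with RDAS as the single primary measure.

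A reader might infer that each scale is to be tested at 0.05 and that the trial's error rate is therefore 18.5%. The article does not say so. Alpha 0.05 appears once, in the RDAS calculation, and no rule makes success on any one scale sufficient. Under an all-of rule error stays at or below 5%, and under a fixed order starting with RDAS both design figures hold for RDAS. The absence of a success rule or adjustment is not in itself a fault in an article, since the analysis plan may supply it.

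A reader might also infer that the intimacy named under Hypotheses ("measures of relationship adjustment and satisfaction, dyadic coping, and intimacy") goes unmeasured, or that listing communication as secondary ("Secondary outcomes include improvement in mood (for example, anxiety or depression) and interpersonal communication") clashes with a primary DCI. Neither is established. Most questionnaire items are not shown, so coverage of intimacy cannot be ruled out. The one BCRM item shown is about being able to discuss sensitive issues, and a DCI communication subscale can be secondary to a DCI summary score.

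**Conclusion.** The point stands as an inconsistency in the definition of the primary outcome, and the text is wrong as written. The stated pair of 5% error and 80% power is sound for RDAS alone, to within rounding. For two or four primary scales the pair does not hold under any of the three rules in the table: either error rises above 5% or power falls below 80%.

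How far each figure moves depends on a success rule that the article does not state, on the assumption that the other scales share the RDAS effect size and SD, and on the correlation between scales. The ranges are therefore conditional illustrations and not the trial's actual error rate or power. The inconsistency itself needs none of these assumptions.

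**What to change.** State the same single primary outcome in the abstract, the Measurement section and both paragraphs of the sample size and analysis section: the between-arm difference in RDAS change from T1 to T2 (or RDAS at T2 adjusted for baseline), averaged over the two partners, at two-sided alpha 0.05. This matches the existing sample size. Make DCI, KMSS and MMQ secondary, tested in a fixed sequence or with Holm's procedure.

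The Trial status section says recruitment has been under way since April 2011. DCI is a declared primary in the abstract, so moving it is a substantive change. It should be dated and justified before any outcome data are examined by arm.

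If the sponsor prefers several primary outcomes, the document should list them, state whether one or all must succeed and how alpha is divided, and restate the power. With Bonferroni and the assumptions above, 80% per scale would need about 50 (two scales) or 58 (four scales) couples per arm instead of 40.

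The single-primary option costs a wording change and no extra participants or data. Its drawback is that DCI, KMSS and MMQ can no longer carry the primary claim on their own.
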